# Study protocol of a multicenter randomized controlled trial of mindfulness-based intervention versus relaxation to reduce emotional exhaustion in medical students in France: the “Must prevent” study

**DOI:** 10.1186/s12888-020-02529-9

**Published:** 2020-03-11

**Keywords:** Medical students, Mindfulness, Relaxation, Emotional exhaustion, Psychopathology, Empathy

## Abstract

**Background:**

Medical students are exposed to an emotionally exhausting training/work environment and to stressful academic demands. Consequently, psychopathologies, burnout and suicidal ideation are frequent in this population. These factors can also affect their empathy and quality of care. Therefore, the development and implementation of programs to promote resilience to stress specifically in medical students and the evaluation of their efficiency are a priority. Here, we describe the protocol of the first French study to assess the long-term effectiveness and acceptability of a mindfulness-based intervention (MBI) compared with relaxation training (RT) to reduce emotional exhaustion in medical students.

**Methods:**

This multicenter randomized controlled trial (“Must prevent”) plans to enroll 612 students in the fourth and fifth year of medical studies from nine French universities. After inclusion, they will be assigned randomly to the MBI or RT group. Both interventions are structured around an 8-week program that includes one group class per week and daily at-home exercises. The primary endpoint is the emotional exhaustion score assessed with the Maslach Burnout Inventory at month 12 of the follow-up. Secondary endpoints include anxiety-depressive symptomatology, suicidality, psychoactive substance use, depersonalization, psychological and physical pain, empathy, emotional regulation, self-compassion, mindfulness, quality of life, and program acceptability. Evaluations will be done before and immediately after the 8-week intervention, and at month 6 and 12 of the post-intervention follow-up.

**Discussion:**

If the proposed interventions are well accepted and useful to decrease negative emotions and/or increase wellbeing among medical students, they should be disseminated among this population and even included as part of the training on emotional skills needed for the routine medical practice.

**Trial registration:**

This trial is registered under the number NCT04026594 (July 18, 2019).

## Background

Medical students are exposed to challenging academic demands and to an emotionally exhausting work environment. Consequently, their levels of psychological distress, particularly depression, pathological anxiety, burnout, and suicidal behavior, are higher than in the general population [1–3]. Psychological suffering is rarely verbalized by medical students because this is often associated with weakness, and perceived as a barrier to medical practice [4]. Thus, psychopathology and burnout may persist after the end of the medical studies [5], leading young physicians to begin their careers in suboptimal conditions which may affect service delivery and quality of care [6]. A recent survey on the health of medical students and young doctors in France (*N* = 21,768) illustrate well the above. Results revealed that 68.2% of participants reported pathologic anxiety, 27.7% high level of depressive symptomatology, and 23.7% suicidal ideation [7].

Moreover, the stress of the academic and psychological demands can impair affective abilities, such as compassion and empathy that are important factors for optimal care delivery and successful social interactions in medical settings [8, 9]. There is evidence that empathy tends to decrease during the medical training period [10], compromising the communication with patients and ultimately the physician’s competence. In this context, the development and implementation of prevention programs to promote stress resilience and to develop emotional competences among medical students is a priority.

Mindfulness-Based Interventions (MBI) favor an intentional and non-judgmental awareness of the present moment [11]. Several studies have shown that MBIs have a positive effect on mental health outcomes and on the development of stress management skills and emotional competences [12]. The systematic reviews by O’Driscoll et al. [13] and by McConville et al. [14] explored MBI effect on students’ health and social care and reported positive changes on mood, anxiety, mindfulness levels, well-being, self-efficacy, empathy, self-compassion and coping abilities. Moreover, MBIs are well accepted and even popular among university students, probably because these approaches are perceived as emotional skill training strategies rather than programs addressed to improve mental health outcomes [15].

Relaxation training (RT) is another effective approach to manage stress in different populations [16–18]. Studies on student populations have shown that RT contributes to decrease distress, academic stress, test anxiety, and to increase positive mood [19–21].

Few studies (and none in France) compared MBI efficacy in medical students and in an active control group [13], and only one compared MBI and RT in this population. Jain et al. [20] evaluated the effectiveness of an adaptation of the Mindfulness-Based Stress Reduction (MBSR) program developed by Kabat-Zinn [22] compared with somatic relaxation in students pursuing different medical degrees (*N* = 83). They found that both interventions reduced distress and increased positive mood; however, the MBSR program was more effective in increasing positive states of mind. These preliminary results should be confirmed in larger samples. New studies should include also a long-term follow-up to explore the maintenance of such benefits, which is currently unknown [13].

Here, we describe the protocol of the first multicenter, randomized, controlled trial with one year of follow-up to compare MBI and RT effectiveness in reducing emotional exhaustion and in promoting mental health and emotional skills in medical students in France.

### Aims

The main objective of the “Must Prevent” trial is to evaluate and compare the effectiveness of MBI and RT in reducing emotional exhaustion in fourth- and fifth-year medical students at month 12 of the follow-up after the end of the intervention.

The secondary objectives are:
to compare psychopathological parameters (i.e. anxiety-depressive symptomatology, perceived stress, psychoactive substances consumption, psychological pain, depersonalization, and suicidality), emotional skills (i.e. mindfulness levels, empathy, self-compassion, emotional regulation), and quality of life before and immediately after the intervention, and then at month 6 and 12 of the post-intervention follow-up.to investigate the acceptability and satisfaction of these interventions.

We hypothesized that both interventions will be useful to decrease emotional exhaustion and psychopathological parameters in medical students. However, we think that MBI will be more effective than RT for developing emotional skills, such as empathy, self-compassion and mindfulness.

## Methods

### Design and participants

This is a multicenter, single-blind, randomized, and controlled study. The main inclusion criterion is to be a fourth- or fifth-year medical student. Exclusion criteria include: current depressive episode and/or panic disorder according to the DSM-5 diagnostic classification [23], and refusal to participate.

The study protocol was registered in the Clinical Trials Registry (ClinicalTrials.gov; number NCT04026594, July 18, 2019) and was authorized by the French Health Ministry (ANSM, September 13, 2019), and approved by the French Est I Ethics Committee for the Protection of Patients (June 20, 2019). Figure 1 summarizes the study design.

**Fig. 1 Fig1:**
[figure not shown]
Study Design

### Sample size

The sample size calculation was based on the results of the work by Verweij et al. [24]. In this randomized controlled trial, the mean baseline score of the emotional exhaustion subscale of the Maslach Burnout Inventory (MBIn) [25]. of 148 residents working in one of the medical, surgical or primary care disciplines was 15.6 (SD = 7.5). Assuming that the baseline score distribution will remain unchanged at the end of the trial in the MBI group, 274 students per group are required to show a significant mean between-group difference of 1.8 points for the emotional exhaustion subscale score at the end of the trial (15.6 for the MBI group and 17.4 for the RI group) with a statistic power of 80% and a 2-sided α level of 0.05. The percentage of participants lost to follow-up is estimated at 10%. Therefore, in total 612 students need to be recruited in the nine universities participating in the trial.

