### MBI and RI programs

The MBI is an adaptation of the MBSR program developed by Kabat-Zinn [22]. The intervention will last 8 weeks, with one group session of 150 min per week. It will be delivered according to the fundamental concepts and specific techniques provided in the MBSR manual (e.g. body scan, hatha yoga, sitting, walking, and loving kindness meditation). It will also include up to 45 min of daily exercises at home, but not the full-day silent retreat programmed at week 6 of the course in the original protocol. This retreat will not be done for reasons of feasibility, and to have a similar number of training hours in both groups (MBI and RT). To adapt the program to medical students, discussions on mindfulness and related topics will be contextualized to the specific academic/medical demands.

The 8-week RT program includes one group session of 150 min per week and 45 min of daily at-home exercises. After an introduction about relaxation and its usefulness, participants will learn relaxation techniques classified in three types: relaxing breathing techniques (e.g. abdominal breathing), muscle relaxation (e.g. Jacobson’s progressive relaxation technique), and cognitive relaxation (e.g. guided imageries).

In both interventions, participants are encouraged to perform training exercises at home every day and to fill in worksheets to keep a record of their training and promote self-observation. A recall MBI and RT group session will be proposed at month 6 after the intervention end to strengthen their motivation and to avoid forgetting the techniques.

MBI and RT group sessions will be carried out by accredited (in the case of MBSR) and experienced instructors (two instructors per center).

Although no risks are expected for both interventions, participants will be encouraged on enrolment to look for signs of their health deteriorating, related or no to MBI/RT interventions. If any physical or mental symptom emerges, participants will be referred to relevant health services and/or the research team will contact the preventive medicine of the concerned faculty.

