### Statistical analyses

Demographic data and baseline characteristics will be presented for the whole population and for each intervention group. Categorical variables will be described as numbers and percentages, and quantitative variables as mean and standard deviation or median and range, according to their distribution (normal or not).

The MBIn emotional exhaustion subscale score (primary endpoint) will be compared in the two groups at the end of the trial. An analysis of covariance will be performed including the baseline emotional exhaustion subscale score and baseline covariates that are found to be significantly different in between-group comparisons. If the conditions for carrying out a covariance analysis are not met, the continuous variable will be dichotomized and logistic regression models will be implemented.

The same methodology will be used to analyze the secondary endpoints at visit 4.

Mixed models will be used to study variations (intra- and between-group) of each variable during the follow-up. All statistical analyses will be performed using SAS® (SAS Institute, Cary, NC, USA) and the significance level will be set at *p* < 0.05.

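### Both arms are taught in classes, but the sample size and the stated primary ANCOVA treat students as independent, so 80% power and 5% error rest on an unstated zero class correlation

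*Protocol article*

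**What the plan says.** The Sample size section takes the emotional exhaustion score of a cited trial, whose mean at baseline "was 15.6 (SD = 7.5"), and sets end-of-trial means of "15.6 for the MBI group and 17.4 for the RI group". It concludes that "274 students per group are required to show a significant mean between-group difference of 1.8 points", "with a statistic power of 80% and a 2-sided α level of 0.05". "The percentage of participants lost to follow-up is estimated at 10" per cent, and so "in total 612 students need to be recruited in the nine universities participating in the trial". No ICC, class size or design effect enters.

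The section on the two programmes describes eight weekly group sessions of 150 minutes in each arm and a recall group session at month 6. It adds: "MBI and RT group sessions will be carried out by accredited (in the case of MBSR) and experienced instructors (two instructors per center"). The Procedure section has individual 1:1 allocation by minimisation.

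The Statistical analyses section specifies the primary model: "An analysis of covariance will be performed including the baseline emotional exhaustion subscale score", together with baseline covariates found to differ between the groups. It mentions mixed models only for variation of each variable over follow-up, and names no class or instructor effect there either.

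**The concern.** This is an individually randomised trial with group-delivered treatment in both arms. After randomisation, students in one class share an instructor, peers and a timetable, so their later scores may be correlated. Each class belongs to one arm, so class effects do not cancel in the MBI–RT comparison as centre effects largely do when both arms run in every centre. Stratifying by centre therefore does not deal with them.

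Two things are at stake. A model that ignores positive class correlation gives too small a standard error for the primary comparison, and so too many false positives. And the stated power belongs to neither the planned ANCOVA nor a class-adjusted version of it. The Discussion would use confirmed benefits to argue for placing one or both programmes in the medical curriculum, so an anti-conservative primary test matters.

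**Working it through.** **1. The plan's own figure.** Inputs from Sample size: difference 1.8, SD 7.5, two-sided α 0.05, power 80%.
- SE with 274 per group = 7.5 × √(2/274) = 0.641; noncentrality = 1.8/0.641 = 2.81.
- Noncentral-t power is 79.9% at 273 and 80.07% at 274 per group. So 274 is the smallest n for independent observations.
- Loss of 10%: 274/0.9 = 304.4, rounded up to 305 per group, 610 in total, against the stated 612 (= 9 × 68). The allowance for loss uses up the whole inflation, and nothing is left for a design effect.

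**2. Assumed class sizes.** The protocol gives none. 612/9/2 = 34 enrolled per arm and centre; 274/9 = 30.4 analysed. I take m = 30 (one class or one instructor per arm and centre), m = 15 (two classes) and m = 10 (three). That gives 9, 18 and 27 classes per arm, and 16, 34 and 52 class-level degrees of freedom (df = 2 × classes per arm − 2). Assumed ICC: 0.01, 0.02 and 0.05, as a share of total outcome variance.

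**3. Formulas.**
- Design effect DE = 1 + (m − 1) × ICC.
- Type I error when classes are ignored = 2 × [1 − Φ(1.96/√DE)].
- Power of a class-adjusted analysis: noncentral t on class-level df, with SE = 0.641 × √DE and no baseline gain.
- The same with an assumed baseline–outcome correlation r = 0.5: replace DE by 1 − r² + (m − 1) × ICC. Baseline adjustment reduces individual variance but not a class effect that arises after baseline.

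Example, m = 15 and ICC 0.02: DE = 1 + 14 × 0.02 = 1.28. Type I error is 8.3%. SE = 0.641 × √1.28 = 0.725, noncentrality 2.48, power 67.5% on 34 df. With r = 0.5 the factor is 0.75 + 0.28 = 1.03 and power is 76.7%.

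**4. Results for ICC 0.01 / 0.02 / 0.05.**

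| m | DE | Type I error, classes ignored | Power, no baseline gain | Power, r = 0.5 |
|---|---|---|---|---|
| 10 | 1.09 / 1.18 / 1.45 | 6.0 / 7.1 / 10.4% | 75.2 / 71.8 / 62.9% | 85.3 / 81.6 / 71.1% |
| 15 | 1.14 / 1.28 / 1.70 | 6.6 / 8.3 / 13.3% | 72.4 / 67.5 / 55.3% | 82.4 / 76.7 / 62.0% |
| 30 | 1.29 / 1.58 / 2.45 | 8.4 / 11.9 / 21.1% | 64.2 / 55.6 / 39.3% | 73.4 / 62.9 / 42.9% |

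With ICC 0 and r = 0.5, power would be about 90%.

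**5. Check by simulation.** An ANCOVA on baseline without a class term (5,000 trials per setting, r = 0.5) rejected a true null in 6.6 / 9.5 / 16.0% at m = 15 and 9.0 / 14.5 / 25.2% at m = 30. At ICC 0 it rejected in 4.8% and 4.5%. Adjusting for baseline does not repair the type I error. It raises it slightly, because class variance becomes a larger share of what remains.

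**The case against.** The strongest reply is that this article condenses a fuller protocol and that an analysis plan, not shown, may hold the random effects and degrees of freedom. That is fair as far as it goes. But the article does state a primary model and its covariates, and a class term added later would change that model. Nor could it give the published 274 and 80% a basis other than independence.

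A second reply is that the ICC may be small for a self-reported score taken 12 months after the classes end, and that leaving out the baseline gain is a common conservative choice. This stands in part. With r = 0.5 and ICC 0.01, power is above 80% for classes of 10 or 15. It answers only the power question, not the type I error.

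Third, the worst figures need ICC 0.05 together with 30 students per class or instructor. That also stands: nothing in the protocol fixes either. Recruitment was still open at submission, which may point to several intakes and smaller classes but does not prove it.

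**Conclusion.** The point holds in a conditional form. The 274 assumes independent students although both arms are taught in classes, and the ANCOVA as stated carries the same assumption into the primary test. For any class ICC above zero, that ANCOVA has type I error above 5%. On the assumed ICC range of 0.01 to 0.05 it is about 6.0–10.4% for classes of 10, 6.6–13.3% for classes of 15, and 8.4–21% if one class or instructor serves each arm and centre. The 80% is not the power of the planned analysis. A class-adjusted analysis has about 75–63%, 72–55% or 64–39% without baseline gain, and about 85–71%, 82–62% or 73–43% with r = 0.5.

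A reader might infer that the trial is underpowered, or that its 5% error rate certainly fails. The protocol does not support either: it gives no ICC, class size or baseline correlation, and power could be above or below 80%. A reader might also infer that instructor is confounded with arm within each centre. That would follow only if the two instructors are split one per arm, which the protocol does not say.

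**What to change.** 1. Record class and instructor ID for every participant. The protocol does not show that these are held, and recruitment is under way, so capture should begin at once and be completed for classes already run.
2. Fit the primary ANCOVA as a linear mixed model with a random intercept for class (or for instructor within arm and centre) and Kenward–Roger or Satterthwaite degrees of freedom. Carry the same term into the longitudinal mixed models. Write this in before outcome data are compared by arm.
3. Replace the single 80% with the power of 274 per group under a stated ICC, class size and baseline correlation, shown as a range. No extra recruitment is proposed.

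The cost is two ID variables to capture, some analysis wording, and a stated power that may fall below 80%.

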### Procedure

Recruitment will take place in nine French medical universities (Montpellier, Paris, Marseille, Nîmes, Strasbourg, Clermont-Ferrand, St Etienne, Angers and Tours) where the study will be advertised and students will receive general information. Students interested in participating will be included after verification of their eligibility and after signing an informed consent form obtained via the investigators. Participants will be randomized to the MBI or the RT group by an independent researcher, not otherwise involved in the study. Randomization will be stratified by study center and degree of emotional exhaustion (MBIn emotional exhaustion subscale score < 17, 18–29, and ≥ 30 [25, 26]). Randomization will be centralized, accessible online and programmed using the Capture Software System (EnnovClinical randomization module) according to a minimization algorithm with a 1:1 ratio.

Participants not included in the study because of a current depressive episode or panic disorder will be referred to the psychological unit of their university.

Participants will be evaluated at four time points (Fig. 1): before (i.e. within 6 weeks) the intervention (visit 1), within the month after the intervention end (visit 2), and at month 6 (visit 3) and month 12 (±1 month; visit 4) of the post-intervention follow-up. Raters will be blind to the allocation (simple-blind). Research assistants and MBI/RT instructors will emphasize the importance of blinding to participants and will repeatedly remind them not to reveal their intervention type. In case of unblinding, another assessor will repeat the entire measurement.

A monetary compensation (40 euros) will be given to participants after each follow-up visit (visits 2 to 4) for the time devoted to the study.

### MBI and RI programs

The MBI is an adaptation of the MBSR program developed by Kabat-Zinn [22]. The intervention will last 8 weeks, with one group session of 150 min per week. It will be delivered according to the fundamental concepts and specific techniques provided in the MBSR manual (e.g. body scan, hatha yoga, sitting, walking, and loving kindness meditation). It will also include up to 45 min of daily exercises at home, but not the full-day silent retreat programmed at week 6 of the course in the original protocol. This retreat will not be done for reasons of feasibility, and to have a similar number of training hours in both groups (MBI and RT). To adapt the program to medical students, discussions on mindfulness and related topics will be contextualized to the specific academic/medical demands.

The 8-week RT program includes one group session of 150 min per week and 45 min of daily at-home exercises. After an introduction about relaxation and its usefulness, participants will learn relaxation techniques classified in three types: relaxing breathing techniques (e.g. abdominal breathing), muscle relaxation (e.g. Jacobson’s progressive relaxation technique), and cognitive relaxation (e.g. guided imageries).

In both interventions, participants are encouraged to perform training exercises at home every day and to fill in worksheets to keep a record of their training and promote self-observation. A recall MBI and RT group session will be proposed at month 6 after the intervention end to strengthen their motivation and to avoid forgetting the techniques.

MBI and RT group sessions will be carried out by accredited (in the case of MBSR) and experienced instructors (two instructors per center).

Although no risks are expected for both interventions, participants will be encouraged on enrolment to look for signs of their health deteriorating, related or no to MBI/RT interventions. If any physical or mental symptom emerges, participants will be referred to relevant health services and/or the research team will contact the preventive medicine of the concerned faculty.

### Assessments

At visit 1, the Mini International Neuropsychiatric Interview (MINI 7 [27]) will be administered to assess mental disorders according to the DSM-5 criteria and to identify participants with current major depression or panic disorder (exclusion criteria). In addition, depression intensity will be assessed with the Montgomery Asberg Depression Scale (MADRS [28, 29]), and suicidality using the Columbia–Suicide Severity Rating Scale, (C-SSRS [30]). Data on the participants’ sociodemographic characteristics (i.e. age, sex, marital status, educational level), and access to psychiatric care (i.e. past psychiatric hospitalization, previous visit to a psychiatrist, psychologist or general practitioner for psychological reasons, previous psychotherapy, and current medications) will also be collected.

In addition to this hetero-evaluation, participants will be asked to complete a set of self-questionnaires to assess the primary and secondary endpoints:

